The third aim is to identify potential mediators of the interventions. Psychosocial constructs measures related to fatigue and physical activity (e.g., self-efficacy, goal-setting, and outcome expectations) will be administered to help identify the underlying mechanisms of the interventions’ possible effectiveness. Our hypothesis is that scores on these measures will significantly improve, and that improvements will explain the interventions’ effect on fatigue and physical activity.

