##### Secondary dependent variables

Health-related quality of life, mental health, and participation in life roles will be measured with the SF-12, Mental Health Inventory, and Community Participation Indicator (CPI), respectively. The SF-12 and Mental Health Inventory are valid and reliable measures, and are commonly used in the population with MS
[43]. The CPI is a new measure developed by Heinemann and colleagues. The measure was developed with input from multiple stakeholders, and has been validated through Rasch analysis in a sample of 1,163 individuals with a variety of disabling conditions
[31,32]. In a subsequent online survey study, the measure had good test-retest reliability over a 2.5 month period in people with MS (t = 0.12, p = 0.91; r = 0.84, p < 0.01). For each item, respondents rate the frequency of engagement (either in days, hours, or times per week, depending on the type of activity), whether it was important (yes/no), and whether they were doing it not enough, enough, or too much. Examples of the 20 items included are: work for money, provide care for a loved one, volunteer, and participate in learning activities.

Six questionnaires will be implemented to identify underlying mechanisms of the interventions’ possible effectiveness for increasing physical activity levels and reducing fatigue impact. Psychosocial construct measures for physical activity will be the Self-Efficacy for Exercise Scale
[44], Exercise Goal-Setting Scale
[12,45], and Multidimensional Outcome Expectations Scale
[46]. All three questionnaires are validated and have been used in previous MS research on physical activity
[45,47]. Psychosocial construct measures for fatigue management will be the validated Self-Efficacy for Performing Energy Conservation Strategies
[48] along with two additional measures on goal-setting and outcome expectations, which will be developed and validated during the study.

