##### Data management and analysis

A secure online application, Research Electronic Data Capture
[49], will be used to manage recruitment efforts and facilitate data collection. The first step in the analysis process will be to compute summary statistics, calculate outcome scores, and conduct quality control assessments. The second step in the analysis will be to test whether the randomization process resulted in equivalent groups at baseline. If differences are found at baseline, these variables will be used as covariates during the hypothesis testing phase. The third step in the analysis process will be addressing normality assumptions, and the potential for missing data, before hypothesis testing begins. If the normality assumption is violated, then an appropriate data transformation will be used. Missing data will be treated conservatively. If appropriate, maximum likelihood, multiple imputation, or last observation carried forward will be used to estimate the missing values. After addressing issues of attrition and missing data, the fourth step will be to conduct intent-to-treat analysis to test the hypotheses. Linear mixed-effects models will be used as the primary analysis tool for testing hypotheses, which include condition, time, and interactions as the fixed covariates, and a random intercept that models the correlation among outcomes collected from the same subject. The mixed models will allow us to determine whether there are significant differences between the three conditions and whether there are significant differences across time. All tests will be two-sided, and p = 0.05 will serve as the criterion for significance. As is typically the case for mixed-effects analyses, the results will not be controlled for multiple comparisons. The generalized estimating equation approaches will be used if the normality distributional assumption is violated for the random effects in the mixed models. To test for mediation, we will use a linear regression model. This analysis will first involve regressing changes in fatigue impact or physical activity on the intervention conditions, and then regressing changes in fatigue or physical activity on the intervention conditions plus changes in the potential mediator. Mediation will be based on the interventions’ association with physical activity or fatigue impact being reduced in magnitude and non-significant after controlling for the mediator variable.

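### The Aim 3 mediation rule takes a smaller, non-significant direct effect as proof of mediation and bases nothing on the indirect effect

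*Protocol article*

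**What the plan says.** Specific aim 3 (Background) is to identify potential mediators. Its hypothesis is that "scores on these measures will significantly improve, and that improvements will explain" the interventions' effect on fatigue and physical activity. Under Secondary dependent variables: "Six questionnaires will be implemented to identify underlying mechanisms" of the interventions.

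Data management and analysis then sets out two linear regressions. The first step: "This analysis will first involve regressing changes in fatigue impact or physical activity on the intervention conditions". The second is described as "regressing changes in fatigue or physical activity on the intervention conditions plus changes in the potential mediator". The decision rule follows: the condition association must be "reduced in magnitude and non-significant after controlling for the mediator variable".

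The text does not say that the first-step effect must be significant. It attaches no criterion to the mediator's coefficient and names no test or interval for the indirect effect. On error control, the same section says "All tests will be two-sided, and p = 0.05 will serve as the criterion for significance" and that "the results will not be controlled for multiple comparisons".

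**The concern.** This is a stated decision rule, not a detail left for an analysis plan, and it has two faults.

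- **Non-significance is read as absence.** If part of the effect bypasses the mediator, the direct effect can be non-significant simply because the trial is small. With more data it becomes significant, and the same true mediator is then rejected.
- **The quantity Aim 3 is about does not enter the verdict.** The indirect effect is the product of the condition effect on the mediator and the mediator effect on the outcome. An irrelevant mediator can pass: it shrinks the condition coefficient by chance about half the time, and if the treatment moves it, collinearity widens the standard error of the condition coefficient.

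At stake is which psychosocial constructs the trial reports as explaining its effect.

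**Working it through.** The protocol gives no power, error rate or sample size for the mediation analysis, so there is no stated figure to reproduce.

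**Inputs from the protocol (Sample size; Data management and analysis).** 63 per arm with 20% attrition: 63 × 0.8 = 50.4, so about 50 analysed per arm. Effect size 0.6. Two-sided alpha 0.05.

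**Assumptions (no document gives them).** One active arm versus control; within-arm SD of change scores 1; *a* = condition effect on the mediator, *b* = mediator effect on the outcome, *c′* = direct effect; total = *c′* + *ab*.

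**Standard errors with n per arm.**

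- Total effect: SE = √(2/n). At n = 50 this is √0.04 = 0.20, so 0.6/0.20 = 3.0.
- Direct effect: SE ≈ σ√[(2/n)(1 + a²/4)], where σ² = 1 − b² is the residual variance. The factor (1 + a²/4) is the collinearity cost. At a = 1.5 and b = 0 the SE rises from 0.20 to 0.20 × √1.5625 = 0.25.

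**Mediator with no effect on the outcome (b = 0, c′ = 0.6, n = 50).** At a = 0, P(direct effect non-significant) ≈ Φ(1.96 − 3.0) = 0.149. The coefficient shrinks about half the time, giving 0.149/2 ≈ 7.5%. With no treatment effect at all, 0.95/2 ≈ 47%. Simulated shares of all trials that declare mediation:

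| Mediator shift *a* (SD) | Rule as written | Significant total effect also required |
|---|---|---|
| 0 | about 8% | about 1% |
| 0.5 | 12% | 4.2% |
| 0.6 | – | 5.3% |
| 0.8 | 15% | 7.5% |
| 1.0 | 18% | 10% |
| 1.5 | 26% | 19% |

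With no treatment effect and *a* = *b* = 0, the rule as written fires in about 47% of trials (0.4% with the added requirement). A joint test, requiring both *a* and *b* to be significant, stays at or below about 5% throughout.

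**Half-mediated effect (a = 0.8, b = 0.375, c′ = 0.3).** Here *ab* = 0.3, half of 0.6, and σ² = 1 − 0.375² = 0.859.

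- n = 50: SE = √(0.859 × 0.04 × 1.16) = 0.200; c′/SE = 1.50; Φ(1.96 − 1.50) = 68%.
- n = 100: SE = 0.141; c′/SE = 2.12; Φ(−0.16) = 43%.
- n = 200: SE = 0.0998; c′/SE = 3.00; Φ(−1.04) = 15%.

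Simulation of the rule as written gives about 69%, 44% and 16%. These figures carry a point or two of simulation error and depend slightly on the variance convention.

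For the joint test at n = 50: a/SE = 0.8/0.20 = 4.0, and b/SE = 0.375/√(0.859/100) = 4.05. The chance that both are significant is about 0.98 × 0.98 = 96%. Simulation gives about 95%, and about 100% from n = 100.

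**Other paths.** With a = 0.6, b = 0.5, c′ = 0.3, the rule declares mediation in 62%, 36% and 9% at 50, 100 and 200 per arm; the joint test does so in 84%, 99% and 100%. With a = 0.4, b = 0.3, c′ = 0.48, the rule gives 31%, 7% and 0.2%; the joint test gives 43%, 80% and 98%.

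**Full mediation (c′ = 0, a = 0.8).** With total 0.4, the rule rises from 73% at n = 20 to 83% at 50 and 95% at 200. With total 0.6, it rises from 86% at 20 to 95% at 200.

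**The case against.** The best defence is that Aim 3 asks whether improvements explain the effect, which can be read as a question about complete mediation. On that reading, rejecting a half-mediator as data accumulate is no error, and under full mediation the rule improves with sample size. This stands in part. But the rule still accepts the absence of a direct effect on non-significance alone, and partial mediation gets no verdict.

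Some stronger conclusions a reader might draw are not supported:

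- *Loss of significance alone suffices.* The rule also requires a smaller coefficient.
- *Less data always means more mediation.* This fails under full mediation, and with no effect at all the rate is flat near 46–47%. If a significant total effect were required first, the half-mediated rate would be hump-shaped: about 31%, 53%, 44% and 16% at 20, 50, 100 and 200 per arm.
- *False findings are frequent in every setting.* With a significant total effect required, the rate passes 5% at 50 per arm only for mediator shifts of roughly 0.6 SD or more. At 63 per arm it is 3.3% for 0.6 SD and 5.7% for 0.8 SD. No document states a mediator shift.
- *The condition effect on the mediators goes untested.* Aim 3 hypothesises that the scores improve, the questionnaires are listed with the secondary variables, and mixed models are the stated tool for testing hypotheses. A separate test is therefore plausible; the mediation verdict just does not depend on it.
- *The trial's main conclusions are at risk.* Aims 1 and 2, the sample size and data collection do not use this rule.

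**Conclusion.** The concern holds in this form: the written criterion treats a smaller, non-significant direct effect as mediation and ties no estimate or test of the indirect effect to the claim.

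At the planned size the errors run both ways. Read literally, the rule accepts an irrelevant mediator more often than 5% at 50 per arm whatever the mediator shift. It also misses roughly three in ten half-mediators (100 − 69 = 31%), where a joint test misses about one in twenty, and that gap widens with more data. Reading in a significant total effect removes most false acceptances for small mediator shifts, but it lowers detection of the half-mediated case to about 53%.

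The exact rates rest on the assumed paths and on one active arm versus control, per mediator. The direction of the fault when a direct effect remains does not. This should be fixed before analysis, for Aim 3 only.

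**What to change.** Replace the criterion in Data management and analysis. For each mediator and each active-versus-control contrast:

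1. Regress mediator change on condition (path *a*).
2. Regress outcome change on condition plus mediator change (path *b* and the direct effect).
3. Report the indirect effect *a* × *b* with a bootstrap 95% confidence interval, and claim mediation only if that interval excludes zero.
4. Report the direct effect with its confidence interval, and delete the requirement that it become non-significant.

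The cost is a change of wording, plus one extra regression and a bootstrap per mediator and contrast. All of it uses data the trial already plans to collect.

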## Discussion

Possibly the most overlooked determinant of a poor quality of life and participation restrictions in adults with MS involves the cyclical relationship between fatigue and inactivity, and the subsequent development of secondary conditions. Research indicates that fatigue is a common and profound barrier to engaging in physical activity among persons with MS
[16,17], and that inactivity is related to functional decline
[50]. Furthermore, in a recent longitudinal study, Motl et al.
[18] demonstrated that changes in both fatigue and depressive symptoms are significantly associated with reduced physical activity levels. Finally, we note that many studies indicate that MS fatigue and inactivity negatively affect quality of life and participation in life roles
[51-55]. Together, these studies suggest a cyclical relationship between fatigue and inactivity, and that it reduces quality of life and increases participation restrictions. Thus, there is a need to conduct cross-disciplinary research that fills the existing gap in the MS literature regarding whether combining fatigue management with physical activity promotion has beneficial synergistic effects on increasing quality of life and reducing participation restrictions in persons with MS.

The proposed interventions are expected to have beneficial effects on participants regardless of the cause of MS fatigue. Although the pathophysiology of MS fatigue remains unclear, researchers distinguish between primary and secondary causes of MS fatigue
[14]. Primary causes of fatigue pertain to MS pathology and adaptive responses, such as brain lesions, axonal damage, cortical reorganization, and neuroendocrine factors
[56-58]. Secondary factors in fatigue pertain to personal characteristics that are not specific to MS, such as de-conditioning and depression. Ultimately, participants in the proposed study may experience fatigue because of primary and secondary factors. The fatigue management program involves teaching compensatory strategies, and physical activity may mitigate secondary factors associated with fatigue
[47]. Thus, we expect the FM+ intervention to be the most effective because of its potential to facilitate engagement in compensatory strategies and address secondary fatigue factors.

Although physical activity may prevent de-conditioning and improve other secondary factors associated with fatigue, such as depression, there is limited research on identifying cost-effective strategies to increase physical activity levels. Encouraging participants over the phone to set realistic goals and self-monitor walking behavior with a pedometer may be a cost-effective and ecologically-valid strategy for increasing physical activity behavior in the population with MS. Since the most common type or mode of physical activity among persons with MS is walking
[6,59], having participants set goals to increase daily walking steps is a practical method for increasing physical activity. Furthermore, Stuifbergen et al.
[60,61] have demonstrated the utility of using goal-setting to promote healthy behaviors in persons with MS. Locke and Latham contend that goal-setting directs attention toward goal-relevant activities and away from irrelevant activities, and helps foster intrinsic motivation
[38]. They posit that personal barriers can impact the efficacy of goal-setting for motivating behavior change. Thus, the development of strategies for overcoming such barriers as fatigue might augment the effect of a goal-setting approach for increasing physical activity.

Nonetheless, we acknowledge there is the risk that a walking program may be ineffective in adults with MS, or that a walking program may result in imprudent risk for injuries. Cold and icy or hot weather, along with other environmental factors such as connectivity of sidewalks, could influence individuals’ ability and willingness to walk. This potential limitation will be addressed by providing information on how individuals with MS can safely engage in a walking program on a regular basis. For example, tips will include taking a cool shower before engaging in physical activity, wearing a cooling vest while engaging in physical activity, or walking in a climate-controlled facility, such as in a mall. We will monitor the frequency of injuries and exacerbations, as well as overall symptom severity and function, with a safety questionnaire. However, moderate-intense physical activity programs are generally considered to be safe for individuals with mild to moderate MS symptoms
[62].

## Conclusions

This study will build upon the work of Stuifbergen et al.
[60], McAuley et al.
[35], and Motl et al.
[45] by implementing a minimal-contact telephone-based intervention; the work of Mathiowetz et al.
[26] and Finlayson et al.
[63] by evaluating the combined benefits of promoting physical activity and teaching fatigue management strategies; and the work of Bombardier et al.
[64] by exploring the effectiveness of changing behavior using a combination of group teleconferences and one-to-one calls without any face-to-face contact. This proposed study represents the largest randomized controlled trial to examine the effects of a lifestyle physical activity intervention in people with MS, and the first study to systematically explore the combined benefits of teaching fatigue management strategies and promoting physical activity. If the teleconference intervention is shown to be effective, future translational research will involve exploring strategies to implement it within clinical care and comparing it to traditional in-person, individualized rehabilitation interventions.

## Abbreviations

MS: Multiple sclerosis; RCT: Randomized controlled trial; FM +: Fatigue management plus physical activity intervention; MHI: Mental Health Inventory; MSIS: Multiple Sclerosis Impact Scale; CPI: Community Participation Indicator; NARCOMS: North American Research Consortium on MS; OT: Occupational therapy.
